##### Feasibility of teaching strategies

To evaluate teachers’ perceptions of the feasibility of implementing relatedness-supportive and class cohesion strategies, the same set of items used to measure their teaching beliefs (e.g., “It is feasible for teachers to foster positive relationships in the classroom”; Aelterman et al., 2014) will be applied. Responses will be assessed using a 5-point Likert scale, ranging from 1 (*totally unfeasible*) to 5 (*totally feasible*).

##### Intention to apply teaching strategies

To evaluate teachers’ intention of implementing relatedness-supportive and class cohesion strategies, the same four-item scale used to assess their pedagogical beliefs will be employed (e.g., “I will promote positive relationships among classmates”; Aelterman et al., 2014). Responses will be assessed using a 5-point Likert scale, ranging from 1 (*no intention*) to 5 (*definite intention*).

##### Evaluation of the training program

A multi-method approach will be used, combining teacher questionnaires, a focus group with teachers, and a mixed-method assessment by an external researcher. This approach seeks to gather both quantitative and qualitative evidence on the program’s effectiveness and implementation. Firstly, consistent with previous studies (Aelterman et al., 2013), teachers will complete a brief questionnaire assessing various aspects of the training program at the end of the first two group face-to-face sessions. The questionnaire comprises items evaluating the training’s acceptability across six dimension: interaction (i.e., “The training was sufficiently interactive”), innovation (i.e., “The training was innovative”), interest (i.e., “The training was engaging and interesting”), clarity (i.e., “The content was easy to understand”), relevance (i.e., “The training was essential for my learning”), and the degree to which they would recommend the training to other educators (e.g., “I would suggest this training to my colleagues”). Responses will be assessed using a 5-point Likert scale, ranging from 1 (*strongly disagree*) to 5 (*strongly agree*).

Secondly, upon completion of the training program and concurrent with the post-test (T2) administration of both teachers’ and students’ questionnaires, all experimental PE teachers will participate in a focus group. The discussions will address the following key topics: (1) the project’s theoretical underpinnings (i.e., SDT and CMC) and their feasibility within the educational setting; (2) the design and application of strategies aimed at fostering relatedness and class cohesion in PE; (3) the pedagogical approach employed (e.g., use of images, videos, practical examples, formative assessment techniques, and interactive exercises) and teachers’ perceptions of their instructional style; (4) perceived changes in the teachers’ variables assessed via questionnaires; and (5) an overall evaluation of the training program (e.g., innovation, practical relevance, feasibility of motivational strategies, intention to implement them, and overall satisfaction). The focus group session will be led by a principal moderator and an assistant, both with expertise in SDT, CMC, PE, and qualitative methods, with no trainers present to encourage open dialogue. The session will begin with an introduction to the aims and process, followed by a brief overview of the key topics. The assistant will handle logistics, take notes, and manage recordings. Finally, the moderator will summarize the main points and confirm with the teachers if the summary reflects their views or if they wish to add anything. The session will be in a neutral, comfortable setting, lasting approximately 60 min. The session will be recorded and transcribed for analysis.

Third and finally, a mixed-method evaluation will be conducted by an external researcher using the same teacher questionnaire (i.e., interaction, innovation, interest, clarity, relevance, usefulness, and feasibility), and will include external observations of the various sessions. This alignment will enable a more in-depth assessment of the training program’s quality by triangulating teachers’ self-reported perceptions with external observations.

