**Figure 1 fig1:**
[figure not shown]
Data collection timeline and overall study design. ^*^Variables measured after the first part of the training program.

To address previous limitations, this study will extend the duration of the teacher training, ensuring that teachers acquire the necessary knowledge and skills to effectively implement relatedness and class cohesion strategies in their classes. To do so, the recommendations proposed by Reeve et al. (2022) for SDT-based training programs will be followed. Additionally, as recommended by Ahmadi et al. (2023), this training program will not only focus on relatedness-supportive behaviors but also on avoiding relatedness-thwarting behaviors, because both have been shown to significantly influence students’ motivational processes and adaptative outcomes (Vasconcellos et al., 2020). Importantly, teachers may learn relatedness supportive strategies while unintentionally maintaining relatedness thwarting behaviors, highlighting the need for awareness and reflection throughout the training. Furthermore, this SDT-based training program will incorporate class cohesion strategies to promote a sense of group belonging, ensuring that all students feel included, which can enhance peer learning and classroom integration.

According to the outcomes, several variables will be selected based on prior evidence identifying them as key motivation- and learning-related constructs (e.g., autonomous motivation, problematic relationships, group processing, learning, or academic performance; Vasconcellos et al., 2020). All study variables will also be examined by sex to determine whether the intervention is equally effective for boys and girls. Finally, a follow-up post-intervention measure will be implemented at the end of the academic year to evaluate the long-term effects of the intervention.

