### Teachers’ training program and implementation phase with students

The intervention will consist of two phases for the experimental group: (1) a face-to-face teacher training phase, which includes two group sessions, one group booster session, and two individual follow-up sessions, and (2) an implementation phase, during which teachers will apply the strategies with their students (see Figure 1).

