##### Face-to-face teacher training phase

The training will be structured into two main parts (see Figure 1) and following the three-phase framework proposed by Reeve et al. (2022): (1) *Get Ready to Work*: theoretical foundations and awareness-building, (2) *How To?*: practical strategy development, and (3) *Peer-to-Peer Group Discussion*: collaborative reflection after implementation. This structure was selected for its evidence-based support in promoting long-term teacher behavior change and alignment with the intervention’s goals.

The first part, which will be conducted in late September, involves two group sessions, each lasting 3 h, that addressed the first two phases (i.e., [1] Get Ready to Work, and [2] How To?). After completing this phase, a round of classroom observations will be conducted to assess the implementation of the proposed strategies. The second part, a booster session, which will be delivered in January, focuses on the third phase (i.e., [3] Peer-to-Peer Group Discussion). This session will be informed by the first observations and teachers’ weekly logs and will be followed by a second round of observations to support teachers’ development and practice integration further. Following this structure, the training sessions will include several activities aimed at enhancing teachers’ theoretical understanding, co-creation of strategies, and practical application, as detailed below.

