#### PE implementation for experimental group students

The implementation phase will last approximately 6 months, from October to the end of March, as we plan to conduct a post-intervention follow-up measure in the final month of the academic year (i.e., June; see Figure 1). During this period, the co-created strategies will be implemented by the experimental group teachers. Relatedness-supportive and class cohesion strategies learned during the training program will be encouraged for implementation in the different teaching units of their annual teaching plan. Efforts will be made to ensure that teachers implement them as much as possible, in terms of variety, frequency, and intensity, in each PE class. The experimental group teachers will implement a common set of strategies; however, teachers will have the flexibility to adapt these strategies to their specific educational context, considering the characteristics and needs of their students. This process will be conducted under the supervision of a research team member.

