### Plan of analysis

A mixed-method analysis will be conducted to evaluate the training program, as well as to assess the impact of its implementation in PE lessons on the study variables for both teachers and students. Regarding the quantitative analysis, first, a descriptive analysis will be conducted to evaluate both teachers’ and the external researcher’s perceptions of the training program, assessing aspects such as its innovation, practical relevance, and the feasibility of the strategies implemented. Second, to assess the impact of the intervention program on the study variables for both teachers and students, the nature of the variables will first be examined through tests of normality, validity, and reliability across the three measurements. Third, the assumptions of independence, linearity, and homogeneity of variance will be verified to ensure the appropriateness of analyses based on the general linear model. Fourth, between-group and within-group differences will be analyzed using repeated-measures multivariate analysis of covariance (MANCOVA). A 3 × 2 (Time × Condition) repeated measures MANCOVA will be performed for both teachers and students, with covariates such as age, sex, teaching experience, type of school, and school location for teachers, and age, sex, sociocultural background, and school grade for students. If parametric assumptions are not met, appropriate non-parametric alternatives such as the Wilcoxon signed-rank test (for within-group comparisons) and the Mann–Whitney U test (for between-group comparisons) will be used. Subsequently, to examine intragender differences of the intervention on study variables, a 3 × 2 × 2 (Time x Condition x Sex) repeated measures MANCOVA will be performed for both teachers and students. To further examine changes in each outcome variable over time (T1, T2, and T3) within each group (experimental vs. control), multiple paired t-tests with Bonferroni correction will be conducted. Effect sizes will be calculated using partial eta squared (*η^2^ₚ*). Effect size thresholds will be interpreted as small (*η^2^ₚ* > 0.01), moderate (*η^2^ₚ* > 0.06), or large (*η^2^ₚ* > 0.14) following Cohen’s criteria. For all analyses, the significance threshold will be set at *p* < 0.05. All statistical analyses will be conducted using IBM SPSS Statistics v.25.0. Finally, a longitudinal structural equation model will be employed through the statistical software Mplus (Muthén and Muthén, 1998-2019) to analyze the predictive relationships between the study variables, allowing for the observation of potential differences at the three specific times (T1, T2, and T3) when data are collected.

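### The teacher acceptability form for Hypothesis 5 is given only after the first two group sessions, so its scores rate part one of the training and not the whole program; its dimension list also differs from the external researcher's form

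*Protocol article*

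**What the plan says.** Under Aim 3, Hypothesis 5 predicts positive perceptions of the training program among experimental teachers on interaction, innovation, interest, clarity, relevance and willingness to recommend it. The section Evaluation of the training program gives the matching instrument and its timing, a short teacher questionnaire "assessing various aspects of the training program at the end of the first two group face-to-face sessions". The caption of Figure 1 is consistent with this, marking some variables with the note "Variables measured after the first part of the training program"; the figure is not shown, so which variables carry the mark cannot be checked.

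The section on the training program and implementation phase defines the training as a phase "which includes two group sessions, one group booster session, and two individual follow-up sessions". The dates are given separately. On the group sessions: "The first part, which will be conducted in late September, involves two group sessions, each lasting 3 h". The booster comes in January, with one individual follow-up before it and one after. On classroom use: "The implementation phase will last approximately 6 months, from October to the end of March".

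Two other sources feed Aim 3. All experimental teachers join a focus group at T2, which the protocol places at the completion of the training. An external researcher attends every training session and completes a form presented as identical to the teachers' form, with this content: "i.e., interaction, innovation, interest, clarity, relevance, usefulness, and feasibility". The Plan of analysis then promises a descriptive analysis of teachers' and the external researcher's perceptions of the training, "assessing aspects such as its innovation, practical relevance, and the feasibility of the strategies implemented".

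**The concern.** The hypothesis is about the program; the ratings are about its opening. When teachers complete the form they have attended the two taught sessions. They have not yet used the strategies over the implementation period, received feedback on an observed lesson, or attended the booster. The Discussion lists the booster and the individual follow-ups among the study's contributions, and these are the components for which no individual teacher rating is planned. Aim 3 exists so that the content can be improved before wider use, and ratings that stop at part one say nothing about whether the later components were well received.

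A second difficulty concerns content. The protocol relies on the alignment of the two forms to set teachers' views beside the external assessment, but the two lists differ. The Plan of analysis also names feasibility of the implemented strategies as something to be described, without saying which instrument supplies it. The acceptability form cannot: feasibility is not among its six listed dimensions, and it is completed before implementation.

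**Working it through.** No sample size, power or error-rate figure bears on this point, and the plan states no number to reproduce. The check sets dates and lists side by side.

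**Step 1: timing.**

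| Event | When | Source in the protocol article |
|---|---|---|
| Group sessions 1 and 2 | Late September | Face-to-face teacher training phase |
| Teacher acceptability form | End of those two sessions | Evaluation of the training program |
| Implementation | October to end of March | PE implementation for experimental group students |
| Individual follow-up 1 | Before the booster | Individual follow-up sessions |
| Booster | January | Face-to-face teacher training phase |
| Individual follow-up 2 | After the booster | Individual follow-up sessions |
| T2 questionnaires and focus group | April | Context and design; Evaluation of the training program |

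The form precedes every row below it.

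**Step 2: coverage.** Contacts in the training = 2 group + 1 booster + 2 individual = 5. Contacts that have happened when the form is completed = 2. Share = 2/5 = 40%. Implementation experienced = 0 of about 6 months.

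The 40% counts contacts, not hours. The two group sessions last 3 h each (6 h in all). The durations of the booster and the follow-ups are not stated, so the share of training time cannot be computed. By content, the first two sessions address two of the three framework phases; the third, peer-to-peer discussion, is delivered in the booster and is not covered.

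**Step 3: the two dimension lists.**

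| Dimension | Teacher form | External form |
|---|---|---|
| Interaction | yes | yes |
| Innovation | yes | yes |
| Interest | yes | yes |
| Clarity | yes | yes |
| Relevance | yes | yes |
| Recommendation | yes | no |
| Usefulness | no | yes |
| Feasibility | no | yes |

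The teacher form has 6 dimensions, the external form 7, and 5 are shared. Unmatched = (6 − 5) + (7 − 5) = 3. A combined list has 6 + 7 − 5 = 8 dimensions.

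**Step 4: where later information could come from.**

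- Focus group at T2: covers the whole program, including feasibility and overall satisfaction, but as one discussion of about 60 minutes analysed thematically. It gives no individual scores on the six dimensions.
- External researcher: sees every training session, but is not a teacher.
- The separate teacher scale on feasibility of teaching strategies: a 5-point scale which, read with the general statement under Measures, is given at T1, T2 and T3. It can supply feasibility ratings after implementation. It asks about the strategies, not the quality of the training, and the Plan of analysis does not link it to the program evaluation.

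**The case against.** The strongest reply is that Hypothesis 5 does not rest on this form alone. Aim 3 is explicitly mixed-method with three named sources, and two of them reach the later stages. With 4–5 experimental teachers, a focus group is a sensible main source, and items on clarity or interactivity are best answered while the sessions are fresh. This stands, and it limits the point.

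Three stronger readings are tempting, and the documents support none of them.

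- A reader might infer that the plan contains a quantitative test of Hypothesis 5 that would be passed on September scores alone. It does not: the Plan of analysis foresees only description of these perceptions, with no test or threshold.
- A reader might infer that the plan can hold no teacher data on feasibility after implementation. The separate feasibility scale falls under the instruments given at all three time points, and the focus group also covers the topic. What is missing is a statement of which source the analysis will use.
- A reader might infer that the planned triangulation breaks down. Five dimensions match, and the protocol describes triangulation as setting teachers' self-reports beside external observations, which does not require the forms to match item by item.

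What the reply does not remove is that no individual teacher rating on the hypothesis's own dimensions is described for the later components, and that two lists presented as one questionnaire differ.

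**Conclusion.** The point holds in a limited form. The acceptability scores matching Hypothesis 5 describe part one of the training (2 of 5 contacts, before implementation) and should not be read as ratings of the whole program. The later parts are covered qualitatively and by the external researcher, not by individual teacher ratings on these dimensions. Separately, the teacher and external forms agree on five dimensions and differ on three, which is an inconsistency in the text to be reconciled.

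This rests on two assumptions: that the form is given once, since no later administration is described, and that the hidden Figure 1 does not show another. The consequence is confined to Aim 3. Hypotheses 1–4, the student outcomes and the randomised comparison are unaffected. It is worth correcting because the correction is cheap, not because the trial's main conclusions depend on it.

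**What to change.** 1. Repeat the brief acceptability form at T2, when experimental teachers already complete questionnaires.
2. For Hypothesis 5, report the T2 scores as the rating of the whole program and the September scores as the rating of part one.
3. Use one list of dimensions on both forms. The simplest is the combined list of eight: add usefulness and feasibility to the teacher form and recommendation to the external form.
4. State in the Plan of analysis whether feasibility of the implemented strategies will come from the separate feasibility scale at T2, the focus group or the added item.

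If the form is not repeated, limit the claim drawn from its scores to the first two sessions, and base any statement about the whole program on the focus group and the external assessment.

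Assuming one item per dimension, the cost is about eight extra items, once, for 4–5 teachers. T2 ratings may be less favourable than those taken straight after the sessions, and they rely on longer recall of the September content. Keeping both occasions, labelled separately, deals with this.

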##### Evaluation of the intervention’s effects on students

The focus group will also explore teachers’ perceptions of how the training program and its implementation may have led to changes in students’ outcomes. To this end, specific questions will be included to gain a qualitative perspective on the possible transfer and effects of the training on students’ educational experience.

#### Students’ measures

Students will self-report their age, sex, sociocultural background, and school grade level.

##### Relatedness-supportive/thwarting behaviors

To assess students’ perception of their teacher’s relatedness-supportive and relatedness-thwarting behaviors in PE lessons, the Teacher Interpersonal Style Questionnaire (TISQ; Leo et al., 2023f) will be used. The scale begins with the stem “In PE classes, my PE teacher …” followed by 24 items (four items per factor). In this study, only the relatedness-support factor (e.g., “…always fosters positive relationships among classmates”) and the relatedness-thwarting factor (e.g., “…creates a classroom atmosphere that I do not like”) will be used. Additionally, to control for the effects of the other two basic psychological needs, one item related to autonomy support (e.g., “…takes our opinions into account when planning lessons”) and one item related to competence support (e.g., “…encourages us to trust in our ability to do things well”) will be included. Responses will be collected using a 5-point Likert scale, ranging from 1 (*strongly disagree*) to 5 (*strongly agree*).

##### Class cohesion

To analyze students’ perceptions of class cohesion, the short version of the Class Cohesion Questionnaire (CCQ; Leo et al., 2023c) will be used. This scale consists of six items (three per factor), assessing task cohesion (e.g., “We are united in class during the development of tasks and activities”) and social cohesion (e.g., “Classmates participate in activities outside of class together”). Responses will be collected on a 9-point Likert scale, ranging from 1 (*strongly disagree*) to 9 (*strongly agree*).

##### Relatedness satisfaction

To evaluate students’ relatedness satisfaction in PE lessons, the Spanish version in PE lessons (Moreno-Murcia et al., 2009) of the Exercise Needs Satisfaction Scale (Vlachopoulos and Michailidou, 2006) will be used. The scale starts with the statement “In PE classes.,” followed by four items grouped under a single factor (e.g., “… I feel that I interact with my classmates in a very friendly way”). Responses will be recorded on a 5-point Likert scale, ranging from 1 (*strongly disagree*) to 5 (*strongly agree*).

##### Relatedness frustration

To measure students’ relatedness frustration in PE lessons, the adapted Spanish version of the Psychological Needs Frustration Scale (Bartholomew et al., 2011), validated for the PE context by Trigueros et al. (2020), will be used. This scale begins with the stem phrase: “In PE classes…” and includes four items (e.g., “I feel other people dislike me”). Students will rate each item on a 5-point Likert scale, ranging from 1 (*strongly disagree*) to 5 (*strongly agree*).

